#### Secondary analysis

The frequency of patients with postoperative infections and intra-abdominal infections will be compared between groups according to the same strategy as the main analysis (bivariate comparisons using Chi-square, multivariate analysis using logistic regression). The number of days without hospitalization at D30 will be expressed as means +/- SD or as medians (IQR) as appropriate. The Kaplan Meir methods will be used to estimate the overall and the disease-free survival curves. The corresponding survival rates will be calculated at 3 years. Median survival will also be calculated and differences between survival curves assessed using log rank test. A Cox regression analysis will be used to assess the impact of potential prognostic factors on overall survival and disease-free survival at 3 years. Subgroup analyses according to the stratification groups (site of surgery, surgical approach) will be performed for exploratory purposes. Descriptive statistics will be used to summarize adverse events and compared between the two groups. Safety analyses will be performed on the safety population which will comprise all randomized patients who consented to participate in the study and who have been given a treatment.

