### Objectives

The primary objective is to assess the impact of a flash dose of preoperative corticosteroids versus placebo on the onset of major complications (Clavien-Dindo > 2) [35] within 30 days after elective curative-intent surgery for digestive cancer.

Secondary objectives are to assess the safety of a preoperative flash of corticosteroids versus placebo and its influence on postoperative and intra-abdominal infections at D30, hospital length of stay and 3-year overall and disease-free survival.

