### Endpoints

The primary endpoint is the frequency of patients with postoperative major complications occurring within 30 days after surgery (D30). Major complications are defined as all complications with Clavien-Dindo grade > 2 [35].

Secondary endpoints are:

the overall survival at 3 years (defined as the time from surgery to death from any cause),the disease-free survival at 3 years (defined as the time from surgery to first documented progressive disease or death from any cause, whichever occurs first),the frequency of patients with postoperative infections occurring within 30 days after surgery and defined according to the CDC (Centers for Disease Control and Prevention) definitions,the frequency of patients with intra-abdominal infections (including anastomotic fistula and intraabdominal abscess) within 30 days after surgery and defined according to the CDC definitions,the hospital length of stay (in the case of death, the patient will be considered as hospitalized until D30),the frequency and the type of side effects, particularly hyperglycemia, electrolyte disorders and wound healing assessed respectively by glycemia and electrolyte panel within the first 24 postoperative hours and clinical inspection at D30 follow-up visit.

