### Follow-up

According to each center’s protocol, a D30 visit will be scheduled between postoperative days 28 and 45. Patients will undergo a clinical evaluation by the surgeon and will be asked about any events occurring since the initial hospital discharge. Any complications occurred since the initial discharge or detected during the examination will be recorded. In case of re-hospitalization between hospital discharge and the scheduled follow-up visit at postoperative D30, all data related to any complications will be collected. Dead patients will be considered to have been hospitalized between the date of death and postoperative D30.

The study will end at 3 years. At the end of the study, vital status (including date and cause of death if appropriate) and information about disease progression (including the date of discovery in case of recurrence) will be collected and recorded for all included patients.

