#### Demographics and baseline characteristics

Patient’s characteristics at baseline will be described in terms of frequencies for categorical variables and in terms of means (+/- standard deviation) or medians (interquartile range) for continuous variables. These characteristics will be compared between groups using Chi squared (or Fisher’s exact test) or t-Test (or Mann-Whitney test) when appropriate.

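### Hospital stay is defined as length of stay but analysed as days without hospitalisation at D30, and the death rule can score a death better than a survivor

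*Protocol article*

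**What the plan says.** The Objectives section of the protocol article lists, among the effects to be assessed against placebo, "its influence on postoperative and intra-abdominal infections at D30, hospital length of stay and 3-year overall and disease-free survival". The Abstract also names length of stay as a secondary endpoint. The Endpoints section defines it, with a rule for deaths, as "the hospital length of stay (in the case of death, the patient will be considered as hospitalized until D30". No upper limit is put on the stay of a survivor.

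The Follow-up section words the death rule differently: "Dead patients will be considered to have been hospitalized between the date of death and postoperative D30". It also foresees readmission: "In case of re-hospitalization between hospital discharge and the scheduled follow-up visit at postoperative D30, all data related to any complications will be collected". It does not say whether days spent in hospital on readmission enter the endpoint.

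The Secondary analysis section does not mention length of stay. Its only sentence on hospital stay is "The number of days without hospitalization at D30 will be expressed as means +/- SD or as medians (IQR) as appropriate".

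**The concern.** A reader who follows the Endpoints section and one who follows the Secondary analysis section would compute different variables. Length of stay ends at first discharge and has no ceiling. Days without hospitalisation at D30 stops at 30 days and, on its natural reading, loses days to readmission.

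The choice can change the message. If the treatment shortened the first stay but led to more readmissions, length of stay would favour it while days without hospitalisation might not. The Discussion expects a shorter hospital stay and the article closes by aiming to show better recovery, so this endpoint carries part of the trial's intended claim. With both variables in the protocol, either could be presented as the secondary endpoint once results are known.

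The death rule is a second weakness. Its purpose is presumably to stop a death from looking like a short stay. If it can still place a death above a living patient, it does not fully achieve that.

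**Working it through.** The plan gives no figure for this endpoint, so there is nothing to reproduce. The check scores hypothetical patients under each section's wording.

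**Conventions (assumed).** Days are counted from surgery. S is the day of first discharge, taken as the index stay. R is the number of readmission days up to D30, counted as hospital days. For a death on day t up to D30, the Follow-up rule adds 30 − t hospital days. Days without hospitalisation are then F = 30 − min(S, 30) − R − (30 − t), the last term applying only to deaths. If the Endpoints rule is read as covering the whole window, any death by D30 has 30 hospital days and F = 0.

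**Survivors: do the two variables agree?**

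| Patient | Length of stay | Days without hospitalisation |
|---|---|---|
| Discharged D10, no later event | 10 | 30 − 10 = 20 |
| Discharged D10, readmitted D15 to D22 | 10 | 30 − 10 − 7 = 13 |
| Stay of 31 days | 31 | 30 − 30 = 0 |
| Stay of 45 days | 45 | 30 − 30 = 0 |

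The first row shows exact complements. The second has the same stay but 7 fewer free days. The last two have different stays and the same number of free days. Among survivors, then, the variables diverge for readmissions and for stays beyond D30 only. The readmission difference depends on R being counted, which the article does not settle.

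**Deaths: what do the two rules give?**

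- In-hospital death on D12: 12 + (30 − 12) = 30 hospital days, F = 0. Both sections give the same answer.
- In-hospital death on D3 against a survivor discharged on D40: on length of stay, 3 + 27 = 30 against 40, so the death has the shorter, better value. On days without hospitalisation both have 0, a tie.
- Discharged D8, died D20. Follow-up rule: 8 + (30 − 20) = 18 hospital days, F = 12. Endpoints rule read over the whole window: 30 hospital days, F = 0. Endpoints rule read as running from the death: 18 and 12 again.
- Survivor discharged on D19: F = 30 − 19 = 11. Under the Follow-up rule the D20 death, with 12, ranks above this survivor.

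**Size of the ambiguity for deaths after discharge.** Shift in an arm mean = (30-day mortality) × (share of deaths after discharge) × (days' difference per death). The article gives neither of the first two, so ranges are assumed: mortality 1% to 5%, share 10% to 50%, with the 12 days from the case above.

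- Low end: 0.01 × 0.10 × 12 = 0.012 days.
- High end: 0.05 × 0.50 × 12 = 0.30 days.

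**The case against.** The strongest defence is that this is a condensed article. The Follow-up sentence may simply give the start date for the Endpoints rule. For most patients the analysed variable carries the same information as length of stay, and a full protocol or SAP may settle the rest. Much of this stands, and it rules out several stronger readings.

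- A reader might infer that the two death rules contradict each other. They agree for in-hospital deaths. They differ only for deaths after discharge, and only if the Endpoints rule is stretched over days when the patient was alive at home. That is an ambiguity, not a contradiction.
- A reader might infer that the lack of a named test is a defect, since for infections the section says "The frequency of patients with postoperative infections and intra-abdominal infections will be compared between groups according to the same strategy as the main analysis" and for survival "differences between survival curves assessed using log rank test". But a condensed article commonly leaves the test for a secondary endpoint to the full protocol or SAP, and nothing says the arms will not be compared. Adverse events are to be compared without a named test too. For continuous variables the article names tests at baseline only: "These characteristics will be compared between groups using Chi squared (or Fisher’s exact test) or t-Test (or Mann-Whitney test) when appropriate". The missing test is not in itself a finding.
- The example of the early death against the day-40 discharge applies to length of stay only; on the analysed variable the two tie.

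What the defence does not answer is that the article fixes two different variables for one endpoint. That is a mismatch in what is stated, not a detail left out. Nor does it remove the ranking of a death after discharge above a survivor, which follows from the Follow-up wording as written.

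**Conclusion.** The point holds in a limited form: the endpoint is not uniquely defined, and its death rule fits neither candidate variable well. The variable mismatch affects patients readmitted before D30 (if readmission days count) and those still in hospital after D30. The death-rule problem affects few patients, and the estimated shift of about 0.01 to 0.30 days in an arm mean rests wholly on the assumed mortality and share of deaths after discharge.

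Two broader conclusions are tempting but unsupported. One is that the mismatch touches all 1200 planned patients; it does not, because of the exact complement noted above. The other is that the objective on hospital stay cannot be answered; summaries by arm of a near-complement of length of stay do bear on it.

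This is a secondary endpoint. The primary endpoint, sample size and alpha are untouched. It should still be corrected, because the choice between the two variables ought to be made before the results by arm are known.

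**What to change.** Name one variable in the Abstract, Objectives, Endpoints, Follow-up and Secondary analysis sections: days alive and out of hospital through D30. State that index and readmission days both count as hospital days and that any death by D30 scores 0. Compare it between arms, by a method that the SAP can specify, and report index length of stay descriptively.

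With this rule no death by D30 can rank above a survivor. A death and a survivor in hospital throughout the 30 days would still tie at 0, which should be acknowledged.

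The cost is mainly wording, in an amendment or the SAP before unblinding; the article describes the trial as ongoing, with recruitment expected to finish in September 2026. One item must be confirmed: that the e-CRF captures readmission and discharge dates. The Follow-up section promises data on complications at readmission but does not mention these dates. If they are not captured, fields would have to be added and dates for patients already followed up retrieved from the centres.

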**Methods:**

The CORTIFRENCH trial is a phase III multicenter randomized double-blind placebo-controlled trial to assess the impact of a flash dose of preoperative corticosteroids versus placebo on postoperative morbidity and cancer-related outcomes after elective curative-intent surgery for digestive cancer. The primary endpoint is the frequency of patients with postoperative major complications occurring within 30 days after surgery (defined as all complications with Clavien-Dindo grade > 2). The secondary endpoints are the overall survival at 3 years, the disease-free survival at 3 years, the frequency of patients with intraabdominal infections and postoperative infections within 30 days after surgery and the hospital length of stay. We hypothesize a reduced risk of major complications and a better disease-survival at 3 years in the experimental group. Allowing for 5% of drop-out, 1 200 patients (600 per arm) should be included.

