### Randomization

Eligible patients will be identified at the preoperative consultation with the surgeon. If the patient meets the eligible criteria, the investigating doctor will present the study. The patient will have a reflection period after the consultation and will be informed of his/her right to withdraw consent at any time without prejudice and without having to justify this decision. After receiving the written informed consent and after verification of the inclusion criteria, the patient will be included.

Patients will be randomized in a 1:1 ratio between 2 groups receiving either 20 mg/kg of intravenous methylprednisolone (experimental group) or an identical-aspect intravenous placebo (control group) at the time of anesthesia induction.

Randomization will be performed online by the investigator using the secure CleanWeb platform at the time of inclusion and stratified on the center, the site of surgery (upper digestive/pancreatic or colorectal cancer) and the surgical approach (scheduled laparoscopic or open surgery).

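### The log-rank test for overall and disease-free survival names no strata although randomization is stratified by site and approach, and no treatment hazard ratio is named; stratifying would be a free gain in efficiency

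*Protocol article*

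**What the plan says.** All references are to the protocol article.

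- **Randomization:** "Patients will be randomized in a 1:1 ratio between 2 groups", and allocation is "stratified on the center, the site of surgery (upper digestive/pancreatic or colorectal cancer) and the surgical approach".
- **Secondary analysis, test:** Kaplan-Meier curves and 3-year rates are planned for overall and disease-free survival. Then: "Median survival will also be calculated and differences between survival curves assessed using log rank test". No strata are named.
- **Secondary analysis, model:** "A Cox regression analysis will be used to assess the impact of potential prognostic factors on overall survival and disease-free survival at 3 years". Treatment arm is neither named as a term nor excluded.
- **Secondary analysis, strata:** site and approach return only here: "Subgroup analyses according to the stratification groups (site of surgery, surgical approach) will be performed for exploratory purposes".
- **Abstract, Methods:** "We hypothesize a reduced risk of major complications and a better disease-survival at 3 years in the experimental group". I read this as disease-free survival, the endpoint defined under Endpoints.
- **Main analysis, for contrast:** binary outcomes get odds ratios with 95% confidence intervals and a supporting logistic regression. Secondary analysis extends that strategy to infections. The survival outcomes get no equivalent statement.

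**The concern.** Upper digestive and pancreatic cancers may carry a different prognosis from colorectal cancers, and the design treats site as important enough to stratify on. Balancing a prognostic factor by design and then leaving it out of the test has two known consequences. The pooled log-rank variance includes between-site variation that the balanced design has already removed, so the test is conservative. And when hazards differ between sites, the marginal hazard ratio is closer to 1 than the within-site hazard ratio. Both reduce the chance of detecting a real effect.

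The effect on cancer outcomes is the novelty claimed in the abstract's Discussion, and the abstract states a directional hypothesis for it. The sample size rests on the 30-day complication rate alone, so survival gets whatever power is left over. A hazard ratio with its interval is also what a reader will need to judge the survival result, and the text does not name one.

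**Working it through.** **1. The plan's own figure.** The article gives no event count, target hazard ratio or power for survival. Its only sample size is 1184 for the primary endpoint (26% vs 18%, 90% power), which can be reproduced:

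n per arm = [1.96·√(2·0.22·0.78) + 1.2816·√(0.26·0.74 + 0.18·0.82)]² / 0.08² = (1.148 + 0.747)² / 0.0064, about 562.

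With continuity correction this is 587 per arm (1174 in total), or 590 (1180) at alpha 0.049. That is within 1% of 1184, and nothing in it concerns survival.

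**2. The comparison.** At each event time the log-rank test takes observed minus expected events in the experimental arm, O − E, with variance V.

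- Unstratified: Z = Σ(O − E)/√ΣV, with all patients in one risk set.
- Stratified: the same sums are formed within each site, added across sites, then divided.

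**3. Inputs.** From the document: 1:1 allocation stratified by site, 1184 analyzable or 1200 included patients, and 3 years of follow-up ("The study will end at 3 years"). Assumed, because the document gives none: control 3-year survival by site (upper digestive/pancreatic first), site mix, a common hazard ratio within sites, and exponential times censored at 3 years. Tests are two-sided at 5%.

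**4. Simulation with 600 per arm, site mix equal in both arms, 30% to 50% upper digestive/pancreatic, 4000 runs per scenario, hazard ratio 0.80.**

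| Control 3-year survival | Power, unstratified | Power, stratified by site | Gain (points) | Type I error, unstratified |
|---|---|---|---|---|
| 60% / 70% | 56–59% | 56–59% | about 0 | 4.7–5.0% |
| 40% / 70% | 60–68% | 64–72% | about 4 | 4.3–4.5% |
| 30% / 80% | 46–58% | 58–71% | 12–13 | 2.0–2.3% |

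At hazard ratio 0.75 the gains are about 0, 2–3 and 8–11 points. The stratified test's type I error is 4.8–5.5% throughout.

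**5. Simulation with 1184 patients, half per site, 2000 runs per scenario, hazard ratio 0.80.**

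| Control 3-year DFS | Power, unstratified | Power, stratified by site | Gain (points) | Type I error, unstratified |
|---|---|---|---|---|
| 40% / 70% | 66.6% | 70.1% | 3.5 | 3.9% |
| 30% / 75% | 61.5% | 71.6% | 10.1 | 3.3% |
| 20% / 80% | 54.1% | 74.4% | 20.3 | 1.7% |

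The mean unstratified hazard ratio is 0.82 at 30%/75% and 0.84 at 20%/80%, against 0.80 stratified. The stratified test's type I error is 5.1–5.8% (Monte Carlo standard error about 0.5 points). Further runs with 1184 patients and 30% to 50% upper digestive/pancreatic give gains of about 0 (60%/70%), 2–4 (40%/70%), 8–9 (30%/75%) and 18–21 points (20%/80%).

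**6. Check by formula.** With D events and 1:1 allocation, power is about Φ(√D·|ln HR|/2 − 1.96), and |ln 0.80|/2 = 0.1116.

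- 60%/70%, half per site, D = 385: 19.62 × 0.1116 − 1.96 = 0.23, so power is about 59%. Simulated: 58.6% unstratified, 58.9% stratified.
- 30%/80%, half per site, D = 505: 22.47 × 0.1116 − 1.96 = 0.55, so power is about 71%. Simulated: 57.9% unstratified, 70.8% stratified.

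The stratified test delivers the power that its events should buy. The unstratified test does so only when the sites are similar.

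**The case against.** The strongest objection is that a journal article condenses the full plan. The text never calls the test unstratified, and an analysis plan that is not shown may add strata and list the Cox terms. That is fair, and it rules out reading the text as a firm decision against stratifying. What remains is that the article goes beyond silence: it names the test, gives the Cox model a different stated purpose, and assigns the strata to exploratory subgroups. Those subgroup analyses do not replace a stratified overall comparison.

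A reader might also infer stronger points that the documents do not support:

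- **That survival will have no effect estimate.** Kaplan-Meier 3-year rates and medians are planned and describe the difference. What is not named is a hazard ratio with its interval.
- **That treatment arm is left out of the Cox model.** The text lists no covariates and does not exclude it.
- **That the planned test is invalid or its hazard ratio biased.** The error is in the conservative direction. A marginal hazard ratio of 0.82 to 0.84 against a within-site 0.80 is largely a different, legitimate estimand.
- **That a loss of 10 to 20 points is to be expected.** It needs 3-year gaps of 45 to 60 points between sites. At a 10-point gap the loss is nil.

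Finally, overall and disease-free survival are secondary, with no power claimed, so no promised power is being missed. That stands, and it limits the weight of the point. The simulations stratify by site only, so no calculation here shows a gain from adding planned approach; the argument for adding it is that the analysis should follow the randomization.

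**Conclusion.** The point holds as an efficiency improvement for secondary endpoints. The survival test names no strata despite randomization stratified by site and planned approach, and no treatment hazard ratio is named. At an assumed hazard ratio of 0.80, ignoring site costs about 0 power points at 60%/70% control 3-year disease-free survival, 2 to 4 at 40%/70%, about 8 to 10 at 30%/75%, and up to about 20 at the extreme 20%/80%. The site survival rates, site mix, hazard ratio and exponential form are all assumptions. The direction is less sensitive to them: stratifying by site lost no meaningful power in any scenario, and the gain grows with the prognostic gap. Type I error of the unstratified test was at or below 5% throughout, so a reader should not infer a false-positive risk or doubt the validity of a positive result.

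**What to change.** - Compare overall and disease-free survival with a log-rank test stratified by site of surgery and planned approach (2 × 2 = 4 strata), using the values recorded at randomization.
- State a Cox model with treatment arm as the effect of interest, stratified by the same two factors, reporting the hazard ratio with its 95% confidence interval.
- Keep the prognostic-factor Cox model as a separate, exploratory analysis.
- Center need not be a stratum: with the 23 institutions given in the Discussion, strata would become sparse.

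The cost is wording in the protocol or analysis plan. No new data, patients or visits are needed, since both factors are already recorded. If the full analysis plan already specifies this, only agreement between the documents needs confirming. Trial status gives September 2026 as the expected end of recruitment; the wording should be fixed before any unblinded survival data are seen.
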